## Abstract

**Background:**

Late recurrence after ablation remains a significant issue in patients with premature ventricular complexes (PVCs) who undergo catheter ablation. In this study, we aimed to test the hypothesis that empirical additional ablation (EAA) would improve the long-term control of PVCs from outflow tracts (OT-PVCs) compared with the approach of limited single point ablation at the assumptive location.

**Methods:**

EASE-PVC study (ChiCTR2200055340) is a prospective multi-center, randomized, and controlled trial designed to assess the effectiveness and safety of empirical additional ablation in patients with OT-PVCs. After successful elimination of OT-PVCs, the patients will be randomized into two groups. In patients randomized to the EAA group, additional lesion applications at sites surrounding the successful ablation site will be delivered empirically. For patients randomized to the control group, no additional empiric ablation will be performed around the successful ablation site. The primary endpoint will be freedom from PVC recurrence at 3 months following ablation, without antiarrhythmic drug therapy.

**Conclusions:**

The EASE-PVC study is designed to compare the effectiveness and safety of two different strategies for ablation in patients with OT-PVCs, namely empirical additional ablation strategy versus conventional single point ablation strategy. This prospective, multi-center, and randomized controlled trial, with comparative data evaluating procedural and long-term follow-up results, aims to elucidate the superiority of empirical additional ablation for the long-term control of OT-PVCs compared with the traditional single point ablation strategy.

**Clinical trial registration:**

Chinese Clinical Trials Registry Identifier: ChiCTR2200055340.

## Background

Catheter ablation has been established as an important treatment strategy for idiopathic premature ventricular complexes (PVCs). Success rates with PVC ablation can range from 50 to > 90%, and can vary based on PVC sites of origin, electrophysiological characteristics, ablation techniques, as well as operator experience [1]. Among the different reported locations, PVCs originating from the ventricular outflow tract (OT-PVCs) are the most commonly seen, and similarly have been the most studied [2–5].

The electrophysiological mechanism of OT-PVCs is thought to be firing from a focal origin resulting from the triggered activity or enhanced automaticity [6]. Theoretically, focal ablation with limited ablation at the assumptive origin, as determined by activation mapping or pace mapping, should destroy the tissue and eliminate the PVCs. However, in real practice, inaccuracies with mapping and catheter movement during ablation may result in inadequate lesions, leading to PVC recurrence. To compensate for these “imperfect” lesions, some operators empirically expand the lesion by burning at sites surrounding the “bull’s eye,” though, the value and safety of delivering empiric additional lesions (insurance burns) remain unproven.

In this study, we aim to test the hypothesis that empirical lesions would improve the long-term control of OT-PVCs compared with the strategy of single point burning at the assumptive location.

## Materials and methods

### Primary objective

This study is designed to compare the effectiveness and safety of empirical additional ablation strategy compared with the control group (strategy of single point burning) in patients with OT-PVCs undergoing first-time PVC ablation.

### Study design

EASE-PVC (ChiCTR2200055340) is a prospective multi-center, randomized, and controlled trial designed to assess the effectiveness and safety of empirical additional ablation in patients with OT-PVCs. Patients with structural heart disease (including ischemic heart disease, dilated cardiomyopathy, hypertrophic cardiomyopathy, left ventricular ejection fraction (LVEF) < 40%, NYHA III-IV status, history of cardiac surgery) and serious hepatic or renal dysfunction are excluded from enrollment. Additionally, individuals with a prior ablation for PVCs will also be excluded. The inclusion and exclusion criteria are listed in Table 1. Central randomization will be assigned in a 1:1 fashion between empirical additional ablation (EAA group) and “bull’s eye” ablation (control group).

**Table 1 Tab1:** Inclusion criteria and exclusion criteria

Inclusion criteria
Age 18–75 years old
PVCs from outflow tract
Symptoms could not be controlled by drugs
Exclusion criteria
Previous heart surgery or any interventional therapy
Structural heart disease
Ischemic heart disease, Dilated cardiomyopathy, Hypertrophic cardiomyopathy, LVEF < 40%, NYHA III-IV status
Serious hepatica or renal dysfunction (AST/ALT > three time of upper limit; SCr > 3.5 mg/dl or Ccr < 30 ml/min)
Had accepted ablation procedure for PVCs
Expectation of life < 1 year
Female during pregnancy or at lactation period

***PVCs***, premature ventricular complexes; ***LVEF***, left ventricular ejection fraction; ***AST***, aspartate aminotransferase; ***ALT***, alanine aminotransferase; ***SCr***, serum creatinine; ***Ccr***, creatinine clearance

### Procedural approach

All antiarrhythmic drugs except amiodarone will be held for at least 5 half-lives before ablation. Amiodarone will be held for at least one half month. All procedures will be performed under local anesthesia.

A 6F quadripolar and a decapolar catheter will be advanced into the right ventricle and coronary sinus, respectively. Intravenous isoproterenol challenge and programmed right ventricular stimulation will be used to provoke the PVCs in the absence of PVCs at baseline.

Three-dimensional mapping will be performed to identify the earliest activation site of PVCs using a 3-dimensional mapping system (CARTO 3, Biosense-Webster Inc., Diamond Bar, CA, USA) system. Pace mapping using CARTO’s PASO module will be performed to identify the target only when PVCs are too infrequent to permit adequate activation mapping. After identifying the target, ablation will be attempted. Ablation will be performed with an open-irrigated tip catheter (Thermocool SmartTouch SF, Biosense Webster Inc. or Thermocool Smart Touch, Biosense Webster, Inc.). If the ablation effectively eliminates the PVCs, a single ablation lesion will be delivered for 60–90 s. Following elimination of the PVC, the surface electrocardiogram will be monitored for at least 10 min to assess for PVC recurrence, followed by a challenge of isoproterenol infusion (2–4 µg/kg·min) and standard programmed ventricular stimulation. If no PVCs are seen at this point, the patient will undergo randomization in a 1:1 manner into either the EASE group or control group. Randomization will be performed by an independent party not involved in the study who will open a sealed envelope. For patients randomized to the EASE group, additional lesion applications will be delivered at sites surrounding the “bull’s eye,” namely the previously effectively ablated point. The number and location of additional lesions will be left to the operator’s discretion based on actual technical and procedural considerations. Typically, 6 lesions will be delivered for consolidation adjacent to the successful ablation site (typically to the outflow tracts and above and below the adjacent pulmonic or aortic valve). Additional empiric ablation lesions will only be permitted in the same chamber. For example, if a PVC is eliminated with ablation from the septal RVOT, additional empiric ablation lesions will only be allowable from the RV or above the pulmonic valve, and left-sided lesions from the aortic cusps will not be permitted. In patients randomized to the control group, no additional empiric ablation will be delivered after the waiting period, and the procedure will be ended. If ablation fails to eliminate the PVCs, or if PVCs recur during the 10 min washout period, repeated mapping and ablation will be performed. In the following two situations, patients will not be randomized and will be categorized into the observational group: (1) The PVCs disappear spontaneously during the procedure and the site of origin or ablation effect are unclear; (2) The PVCs cannot be eliminated by repeated ablation (based on operator’s judgement). A flow-chart summarizing the study protocol has been provided in Fig. 1. In both groups, detailed ablation parameters and results will be recorded.

**Fig. 1 Fig1:**
[figure not shown]
Study flow diagrams. PVCs: premature ventricular complexes; ISO: isoproterenol; RV: Right ventricular; EAA group: empirical additional ablation; Control group: “bull’s eye” ablation

Generally, the maximum ablation power will be adjusted from 30 to 40 w at the discretion of the ablator, with temperature limit of 43 °C and irrigation rate of 17–30 ml/min. In the EASE group, additional ablations will be performed targeting the surrounding area close to the “bull’s eye.” If the successful ablation point was below the pulmonary or aortic valve, the corresponding area above the valve will be allowed to be targeted with empiric lesions, and vice versa.

### Follow-up

After ablation, anti-arrhythmic drugs will be discontinued, and no antiarrhythmic drugs will be allowed during follow-up. All patients will undergo 24-h Holter monitoring at 3 months after the procedure to assess PVC burden.

### Study endpoints

The primary endpoint will be freedom from PVC recurrence (defined as a ≥ 80% reduction of PVC burden) at 3 months following ablation, without antiarrhythmic drug therapy.

Secondary endpoints will include the following: (1) PVC burden at 3 months after ablation; (2) any peri-procedural complications.

### Statistical analysis

Based on the previous studies and our experience [7–9], the expected success rate will be 85% in the control group and 95% in empirical additional ablation. A sample size of 282 subjects (141 in each arm) is likely to be sufficient to detect a clinically important difference between groups using Pearson Chi-square test of proportions with 80% power and alpha of 0.025. Considering that approximately 10% of patients are expected to enter into the observational group based on experience, and accounting for a dropout rate of 1%, we calculate that 315 patients will be needed in this study. Accordingly, competitive enrollment will be initiated at each center. The patients will be randomly assigned to two groups by using permuted blocks with randomized block sizes 2 or 4 to ensure equal numbers in both groups. Randomized assignments will be placed in sealed envelopes and numbered consecutively. Random assignment codes will be generated by statistics professionals using the R version 4.1.1. Continuous variables will be expressed as the means ± standard deviations (normally distributed variables) or medians [25th and 75th percentiles]. Normal distribution will be assessed with the Shapiro–Wilk test. Categorical variables will be expressed as numbers and percentages. Chi-square testing will be used for inter-group comparison of success rate of surgery and a *P* value < 0.05 will be considered statistically significant. Statistical analyses will be performed using R version 4.1.1.

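### The primary chi-square test is valid, but stratifying it on one or two factors known before randomisation would be a near-costless improvement

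*Protocol article*

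**What the plan says.** **Primary test.** The Statistical analysis section states "Chi-square testing will be used for inter-group comparison of success rate of surgery", with significance where "a *P* value < 0.05 will be considered statistically significant". The sample size rests on the same kind of test: "the expected success rate will be 85% in the control group and 95% in empirical additional ablation", and "A sample size of 282 subjects (141 in each arm) is likely to be sufficient" for a calculation "using Pearson Chi-square test of proportions with 80% power and alpha of 0.025".

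**Allocation.** "The patients will be randomly assigned to two groups by using permuted blocks with randomized block sizes 2 or 4". No stratification factor is named.

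**Prognostic factors.** The Background says that success rates of PVC ablation "can vary based on PVC sites of origin, electrophysiological characteristics, ablation techniques, as well as operator experience". That sentence concerns PVC ablation at all locations. The Discussion, writing about outflow-tract ablation, adds that mapping-related factors influence acute and long-term results, and that success may be lower when PVCs are too sparse for activation mapping, whatever the site.

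**Timing.** Under Procedural approach, randomisation comes after mapping, elimination of the PVCs, a waiting period and provocation. Pace mapping is used only where activation mapping is not adequate. In both groups "detailed ablation parameters and results will be recorded".

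**The concern.** The article identifies factors that it believes affect outcome, randomises at a moment when two of them (mapping method and side of the successful site) are settled for every patient, and then fixes a primary comparison that uses neither. Both are therefore legitimate baseline covariates.

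At stake is some precision, and the firmness of a verdict that rests on few events: about 28 failures are expected among 282 patients. If one arm by chance receives clearly more of the harder cases, the unadjusted comparison carries that imbalance into the estimate, whereas a stratified one largely removes it. If the adjusted analysis is not prespecified, choosing it after the imbalance has been seen would be open to challenge.

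**Working it through.** **1. The plan's own figure.** Inputs from Statistical analysis: 85% and 95%, 80% power. The pooled-variance formula, without continuity correction, is

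n = [z(α)·√(2·p̄(1−p̄)) + z(β)·√(p₁(1−p₁) + p₂(1−p₂))]² / (p₂−p₁)², with p̄ = 0.90.

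At one-sided 0.025 (equal to two-sided 0.05): [1.96·√0.18 + 0.8416·√0.175]² / 0.01 = 1.1836² / 0.01 = 140.1, so 141 per arm. Power at 141 is 80.3%. The stated size reproduces for the unadjusted test. (Reading 0.025 as two-sided would need 170 per arm, so the one-sided reading is used here.)

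**2. Expected failures.** 141 × 0.15 + 141 × 0.05 = 21.15 + 7.05 = 28.2, or 28.2 / 18 = 1.6 per centre.

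**3. One stratification factor.** The documents give no covariate strength, so the strata are assumed. Each row is 40,000 simulated trials, 141 per arm, two-sided 0.05, with a common odds ratio giving 95% overall success in the additional-ablation arm. The last two columns cover only the trials, about 1 in 20, where that arm has an excess of worse-stratum patients above 1.645 standard deviations; ranges show repeat runs.

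| Control success, better / worse stratum (share in worse) | Chi-square power | CMH power | Chi-square, imbalanced | CMH, imbalanced |
|---|---|---|---|---|
| factor not prognostic | 81.7% | 81.8% | – | – |
| 90% / 77.5% (40%) | 81.7% | 82.5% | 73–76% | 82–84% |
| 91% / 74% (35%) | 81.5% | 83.0% | 69% | 82% |
| 93% / 66% (30%) | 82.2% | 85.4% | 66% | 85–86% |

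The gains are 0.1, 0.8, 1.5 and 3.2 points. Expressed as odds ratios for failure, the last three rows assume (0.90/0.10)/(0.775/0.225) = 2.6, (0.91/0.09)/(0.74/0.26) = 3.6 and (0.93/0.07)/(0.66/0.34) = 6.8, so the largest gain needs a very strong factor.

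With no treatment effect, overall type I error is about 5% for both tests. Among trials with an imbalance beyond 1.645 standard deviations in either direction, chi-square error is about 6%, 7% and 10% in the three prognostic scenarios, while CMH stays at about 5%.

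**4. Two factors.** Assumed prevalences are 30% and 20%, with 4,000 simulated trials per row (simulation error about 0.6 points). The adjusted analysis here is a standardised risk difference.

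| Odds ratios for failure | Chi-square | Adjusted |
|---|---|---|
| 1 and 1 | 80.1% | 80.3% |
| 1.5 and 1.5 | 82.5% | 83.2% |
| 2 and 2 | 81.5% | 82.5% |
| 3 and 3 | 81.5% | 84.1% |
| 5 and 4 | 81.5% | 86.0% |

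A logistic likelihood-ratio test gives 86.2% in the last row. Type I error was 4.6–4.7% for all methods.

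**5. How much imbalance matters.** For a factor with 30% prevalence, the difference between arms has standard deviation √(0.3 × 0.7 × 2/141) = 5.5 percentage points, or about 7.7 patients. Five extra worse-stratum patients in one arm, with control-arm gaps of 12.5 to 27 points, shift expected failures by 5 × 0.125 = 0.6 to 5 × 0.27 = 1.4, which is 0.4 to 1.0 percentage points of success against a planned difference of 10. The protection therefore matters for larger imbalances: 1.645 × 7.7 is about 13 patients.

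**The case against.** The strongest reply is that nothing here is wrong. The trial is sized with a chi-square test and analysed with one; the test is valid under 1:1 blocked allocation, and its error rate already averages over chance imbalance. That stands in full. It also stands that the expected gain is small, about 1 point at moderate covariate strength, and that the factors may be weaker in this population: only acutely successful outflow-tract cases are randomised, and those with an unclear origin go to the observational group.

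A further reply is that a condensed article may leave stratification and adjusted analyses to fuller documents. This is right as to allocation: a reader might infer that randomisation is unstratified, but the article only names no factor. It does not dispose of the point on the test, because the article states the primary comparison and a plan that follows it would inherit it.

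Several other stronger readings are not supported:
- That site and mapping are strong predictors. The article gives no strength, and its remark on site is not about right- versus left-sided outflow tract. Mapping is the better-documented factor here.
- That a few unbalanced cases could overturn the result. Step 5 of the working shows otherwise, except where the result already lies at the threshold.
- That the burden endpoint ignores baseline. No test is stated for it.
- That repeat ablation bears on the choice of test. It takes place before randomisation, under the same rule for both arms.

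**Conclusion.** The point holds as a recommendation for efficiency and robustness, not as a fault. The chi-square test is valid and correctly sized at 141 per arm. Prespecified stratification on one pre-randomisation factor would add 0 to about 3 points of power, and up to about 5 with two strong factors, with no expected loss of power or type I error control. Its clearer benefit is conditional: in the assumed scenarios it holds power at 82% or more when the arms are markedly imbalanced against additional ablation, where the plain test falls to between 66% and 76%. All of these gains rest on assumed prevalences and covariate strengths. If the factors do not predict outcome, nothing is gained and nothing is lost.

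**What to change.** Before database lock, and without sight of outcomes by arm:
- Make the primary test a Cochran-Mantel-Haenszel test stratified by one or two factors fixed before randomisation: mapping method (activation or pace) and/or right- or left-sided successful site.
- Report a stratified Mantel-Haenszel risk difference with 95% CI, which stays on the planned scale of a difference in proportions.
- Keep the plain chi-square test as a sensitivity analysis.
- Do not enter the 18 centres or the operators as covariates; about 1.6 failures per centre cannot support it.
- As advice only, since no test is stated: compare 3-month PVC burden with adjustment for baseline burden, which the primary endpoint already requires as a percentage reduction.

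The cost is a dated change to the analysis plan and a check that both factors are captured in the procedure record. No extra patients are needed. The article reports the first randomisation on 10/28/2021 and expected completion by the end of 2022, so the change departs from a published primary test and should be documented as such. If outcomes by arm have already been seen, the chi-square test should stay primary and the stratified analysis be reported as supportive.

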### Study organization and status

The study is a trial organized by the First Affiliated Hospital with Nanjing Medical University, Nanjing, China, and 18 centers in China will participate in this trial. The study was approved by the Ethics Committee of the First Affiliated Hospital of Nanjing Medical University (2021-SR-384.A1, Jiangsu Province Hospital) and institutional approval will be obtained from all centers before enrollment. This trial is sponsored by Beijing Xinlian Zhicheng Cardiovascular Health Public Welfare Foundation. Submission to the Chinese Clinical Trial Registry (http://www.chictr.org.cn) was posted on 01/07/2022, and the first patient was randomized on 10/28/2021. Completion of the study is expected by the end of 2022.

## Discussion

Catheter ablation was introduced into the clinical practice for the treatment of OT-PVCs over two decades ago [10]. There is a wide consensus that an extra heart beat is caused by one time of electrical impulse from a focus formed by a cluster of cells with abnormal automaticity [11]. Consequently, the ablation strategy for these idiopathic ventricular arrhythmias is to find the site exhibiting the earliest activation, or a site which demonstrates a perfect match compared with the clinical arrhythmia. These sites felt to represent surrogates of PVC origin. As so, factors influencing the process of mapping will impact the acute and long-term efficacy of PVC ablation. Occasionally, when there is a paucity of PVCs at the beginning of an ablation procedure, activation mapping might not be able to be performed, and in these situations ablation success rates may be lower — independent of the site of origin [12]. Additionally, inaccuracies with mapping may lead to ablation targeting incorrect sites, which may result in remote PVC relapse. Furthermore, slight movement during radiofrequency energy delivery, which is inevitable to some extent, may result in inadequate lesions. Based on these speculations, we hypothesized that empirical additional lesion applications surrounding the index ablation site will compensate the limitations of inaccurate mapping and inadequate lesions, thus improving the long-term control of PVCs.

To elucidate the “net efficacy” of the additional ablation lesions, we set a “blanking period” in each case after a lesion successfully eliminates of the PVC. The “blanking period” is indeed a standard and regularly used protocol to ensure an adequate and effective lesion, and includes 10 min of waiting period and a standard provocation protocol of drug challenge and right ventricular stimulation. Only those patients who demonstrate no PVCs after the “blanking period” will be randomized for the study. However, some situations will be excluded from the randomization. The first is the paucity of PVCs during mapping process, as this will result in difficulty in determining the target. The second situation is in cases where PVCs are unable to be eliminated with ablation. These two situations will be based on operator’s discretion and these patients will be categorized as “observational group” accordingly and their procedural data will be recorded.

To explore the association between the intra-procedure electrophysiological features and long-term control of PVCs, a new electroanatomic model (unpublished data from the First Affiliated Hospital with Nanjing Medical University) for the target electrogram will also be employed into this study. In that model, the characteristics of the target potential, including the prematurity and the morphological features, will be analyzed and correlated to the acute and long-term successful rate of OT-PVCs.

The additional benefit of quantitative ablation in the catheter ablation of PVCs remains uncertain [13–15]. Several studies have shown there to be no additional benefit of contact force sensing technology with regards to acute and long-term success rate of PVCs ablation, while another retrospective study showed that ablation index may be a predictor of long-term efficacy of PVCs ablation [16]. To date, the experience of quantitative ablation for ventricular arrhythmia ablation remains insufficient. Considering the fact that there is no consistent AI recommendation for the treatment of PVC ablation, the study will not introduce AI into the lesion evaluation; however, a contact force range of 5–20 g is set to minimize the ablation variance.

The study focuses on OT-PVCs ablation, whether the result could be extrapolated to the PVCs from other sites needs further studies.

